### Measures

The primary outcome is objectively measured physical activity, defined as physical activity energy expenditure (PAEE, measured in kJ/kg/day). It is assessed using the Actiheart®, a single-piece monitor capable of measuring acceleration, heart rate, heart rate variability, and ECG amplitude for a set time resolution [61]. A sub-maximal exercise test was conducted as part of the Fenland Study and is used for individual calibration of heart rate response [62]. Branched equation modelling is utilised to estimate PAEE [63]. This approach has high validity for estimating the intensity of physical activity [64,65] and overcomes some of the key limitations associated with either accelerometers or heart rate monitors alone [61]. Participants are instructed to wear the monitor for six days and nights continuously, and to carry on with all normal activities during this time. The device is non-invasive, weighs less than 8 g and is worn on the chest attached to standard ECG electrodes stuck directly onto the skin. It is only 7 mm thick (33 mm in diameter), and except for a brief period to change electrodes (every few days) it does not need to be removed. Monitors are also waterproof and can be worn while swimming or showering. These factors make it convenient and discreet to wear. Participants are also asked to complete an Actiheart® log sheet, which indicates the date and time they a) started wearing the monitor, b) removed it (along with the reason) and replaced it again, and c) completed measurement.

All secondary outcomes are measured via self-report questionnaire and are described in detail in Table1. They include self-reported diet, self-reported weight, intentions to be physically active and to engage in a healthy diet, anxiety, diabetes-related worry, self-rated health, and other cognitive and emotional outcomes that are based on the PMT and the CSM.

**Table 1 T1:** Measures used in the Diabetes Risk Communication Trial (DRCT)

**Measure(s)**	**Brief description**	**Stage assessed**			
		**Fenland study**	**DRCT baseline**	**DRCT post- intervention**	**DRCT follow-up**
Demographic characteristics	Sex, age, race/ethnicity, immigrant status, level of education, employment status, and level of income were assessed through self-report.	✓			
Anthropometric, body composition, clinical, physical activity, biochemical, medical history, and lifestyle	Anthropometric (e.g., height, weight, hip and waist), body composition (e.g., precise body fat percentage and distribution using ultrasound and DEXA), clinical (e.g., blood pressure and pulse rate), and physical activity measurements (e.g., heart rate, movement, and oxygen consumption at rest and during a sub-maximal treadmill test) were assessed by trained staff. An oral glucose tolerance test was administered, and two blood samples were taken to assess glucose levels and blood lipids. Medical history and general lifestyle were assessed through self-report.	✓			
Perceived healthy weight	Participants are asked what they think a healthy weight is for them in either stones or kilograms. This measure has been used in previous research [66].		✓		
Perceived weight status	Participants are asked if they think that they are underweight, overweight, or an acceptable weight. This measure has been used in previous research [67,68]		✓		
Perception of diet	1) Participants are asked how much fruit and vegetables they think that they eat compared to people of their age and sex, and answer on a 5-point response scale, ranging from “much less” to “much more”. 2) Participants are asked whether or not they meet the national recommendations for fruit and vegetable consumption. Similar measures have been used in previous research [69,70].		✓		
Perception of physical activity	1) Participants are asked how physically active they think that they are compared to people of their age and sex, and answer on a 5-point response scale, ranging from “much less” to “much more”. 2) Participants are asked whether or not they meet the national guidelines for engagement in physical activity. Similar measures have been used in previous research [71,72].		✓		
History of genetic testing	Participants are asked if they have ever had a genetic test to assess their risk of developing a disease, and if so, to list the disease(s) for which their risk was assessed.		✓		
Process measures	Participants are asked what they think that their risk estimate showed, how accurate they think that their risk estimate is, whether or not they have kept their risk estimate, and whether or not they have discussed their risk estimate with someone. Additionally, participants are asked if they previously had a genetic test to assess their risk of developing a disease, and if so, to list the disease(s) for which their risk was assessed.				✓
Diabetes risk representations*	Assessed using the Brief Illness Perceptions Questionnaire (Brief IPQ) [73]. The Brief IPQ consists of 8 items that address the cognitive and emotional illness representations in the CSM. To capture representations of T2D risk held by healthy individuals, the items have been adapted according to methods used in previous research [74,75]. The Brief IPQ has been shown to have good test-retest reliability and to be highly correlated with relevant subscales of the IPQ-R [73].		✓	✓	
Self-efficacy, response efficacy, and perceived severity*	Assessed using 10 Likert items. Each item includes a statement (e.g., “I am confident that I could be more physically active if I wanted to”) evaluated on a 5-point response scale, ranging from “strongly disagree” to “strongly agree”. These items have been adapted for use in the context of T2D [76,77] and have been used in previous research [78].		✓	✓	
Perceived risk*	1) Participants are asked how likely they think that they are to get T2D in the next 10 years and their lifetime, and first answer on a 5-point response scale, ranging from “very unlikely” to “very likely”, and then on a continuous scale, ranging from 1 to 100. 2) Participants are asked how likely they think they are to get T2D in the next 10 years and their lifetime, compared to people their same age and sex, and answer on a 5-point response scale, ranging from “much less likely” to “much more likely”. These items have been adapted according to recommendations provided by Diefenbach et al. [79], and have been used in previous research [80].		✓	✓	✓
Self-rated health*	Participants are asked if they think that their overall health is excellent, good, fair, or poor. This measure has been used in previous research [81].		✓		✓
Diabetes-related worry*	Assessed using the Cancer Worry Scale (CWS) [82]. The CWS consists of 6 items that assess the frequency of worries about developing cancer and the effect that these worries have on mood and daily functioning. These items have been adapted for use in the context of T2D and have been shown to have acceptable test-retest reliability and good internal consistency [83].		✓		✓
Anxiety*	Assessed using the short-form of the state scale of the Spielberger State Trait Anxiety Inventory (STAI) [84]. The short-form STAI consists of 6 items that comprise the most highly correlated anxiety-present and anxiety-absent items from the full-form of the STAI. Scores obtained using this short-form have been shown to be highly correlated with scores obtained using the full-form of the STAI [84].		✓	✓	✓
Intentions to be physically active and engage in a healthy diet*	Assessed using 4 items. Each item includes a statement (e.g., “I intend to be more physically active in the next 8 weeks.”) evaluated on a 5-point response scale, ranging from “extremely unlikely” to “extremely likely”. These items have been adapted according to recommendations provided by Ajzen [77] and have been used in previous research [78,85].		✓	✓	✓
Self-reported weight*	Participants are asked what their current weight is, without shoes, in either stones or kilograms. Detailed descriptions of the reliability and validity of self-reported weight have been published elsewhere [86].		✓		✓
Self-reported diet*	Assessed using the Food Frequency Questionnaire (FFQ) [87]. The FFQ contains a list of 130 foods, including 12 fruit items and 26 vegetable items. Only the fruit and vegetable items are assessed at follow-up. Detailed descriptions of the reliability and validity of the FFQ have been published elsewhere [87,88].	✓			✓

*Secondary outcomes.

### Statistical analysis

We will use univariate descriptive statistics (means, standard deviations, numbers, and percentages) to summarise the characteristics of the study sample at baseline. All trial analyses will be performed on an intention-to-treat basis (i.e., analysis of data according to randomised study group, regardless of whether or not the intervention was received). Those with missing outcome data will be excluded from the analyses (a complete case approach). If necessary, a sensitivity analysis will be performed to investigate the effect of having excluded participants with missing data for the primary outcome only. We will use a multiple imputation procedure with a ‘missing at random’ assumption to impute missing outcome data [89]. Participants with missing baseline data will be included in the analyses using the missing-indicator method [90].

An analysis of covariance (ANCOVA) regression model will be used to determine if differences exist in mean PAEE at follow-up, adjusted for baseline, between randomised groups. Exploratory analyses will be conducted to examine potential moderators and mediators of the intervention effects on PAEE (i.e., sex, age, body mass index, time since the Fenland Study, and baseline measurements of the trial outcomes). A further subgroup analysis will explore whether a high or low risk estimate moderates the effect of type of T2D risk estimate (i.e., genetic or phenotypic) on PAEE. Similar regression analyses will be used to examine differences in all secondary outcomes. Acceptability will be assessed by summarising recruitment rates, loss to follow-up, and reasons for loss to follow-up. Additionally, differences in responses to questions regarding the perceived accuracy of the risk estimates, as well as the retention and discussion of the risk estimates will be examined.

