### Randomisation, allocation concealment and blinding

In order to ensure equal allocation across the three trial groups, participants are allocated to one of the groups using a blocked randomisation procedure. A statistician without knowledge of participant characteristics created a computer-generated list comprised of blocks of six that contain two of each of the three trial groups per block in a random order. The randomisation list was incorporated into a computer program that members of the study coordination team use for enrolment and automated randomisation of participants. Allocation is concealed from the study coordination team, researchers, and participants until the interventions are assigned. It is not possible to blind participants to which intervention they receive. However, researchers assessing the baseline characteristics of participants and the primary outcome of the trial remain blinded to group assignment. Additionally, an independent, quality assured data-entry company undertakes all data entry unaware of group allocation.

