### Sample size

Estimates used in the sample size calculation were taken from the FAB study, which had a similar sample population and the same primary outcome to that proposed here (i.e., PAEE) [91]. The mean (standard deviation) PAEE at follow-up in the FAB study was 46.2 (15.4) kJ/kg/day, and the correlation between baseline and follow-up was high (0.69). After making a Bonferroni adjustment for multiple comparisons in a three group trial, we determined that in order to detect a between-group difference of 4.1 kJ/kg/day in PAEE at follow-up (which equates to approximately 20 to 25 minutes of brisk walking per day), with a significance level of 1.67% and 80% statistical power, approximately 465 participants will need to complete the trial. Thus, allowing for an attrition rate of 20%, we aim to randomise approximately 580 participants.

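### The one stated sensitivity analysis for missing primary outcomes is optional and assumes missing at random, so beyond what its imputation variables explain it cannot show bias from outcome-related dropout that differs by arm

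*Protocol article*

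**What the plan says.** The Statistical analysis section of the protocol article makes complete case the main approach: "Those with missing outcome data will be excluded from the analyses (a complete case approach". The primary model is ANCOVA of follow-up PAEE on randomised group, adjusted for baseline.

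One sensitivity analysis for missing outcomes follows, restricted to the primary outcome: "If necessary, a sensitivity analysis will be performed to investigate the effect of having excluded participants with missing data". Its method is then given: "We will use a multiple imputation procedure with a ‘missing at random’ assumption to impute missing outcome data". The article does not say what would make the analysis necessary or which variables enter the imputation model. It describes no analysis that departs from missing at random.

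Two nearby statements do not fill the gap. The missing-indicator method is for covariates: "Participants with missing baseline data will be included in the analyses using the missing-indicator method". Attrition is also described under acceptability: "Acceptability will be assessed by summarising recruitment rates, loss to follow-up, and reasons for loss to follow-up".

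Two facts elsewhere bear on the point. The Sample size section plans for loss, "allowing for an attrition rate of 20" per cent. The section on randomisation and blinding states: "It is not possible to blind participants to which intervention they receive".

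**The concern.** A sensitivity analysis is useful when it relaxes the assumption on which the main analysis depends. Complete-case ANCOVA is already valid if follow-up PAEE is missing at random given arm and baseline PAEE. Imputing the outcome under that same assumption with the same variables targets the same quantity, so the two results agree whether or not the assumption is true. A reader could take that agreement as evidence of robustness.

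The assumption fails if willingness to wear and return the monitor depends on how active a participant has become, and does so differently by arm. The article itself gives reasons to consider this:

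- Participants know their allocation.
- The Background suggests that a high genetic risk may induce fatalism and a low one false reassurance. Either could reduce both activity and engagement with follow-up.
- Controls receive no risk estimate until they have completed follow-up, so the incentive to return data is not identical across arms.

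Because the check is conditional without a criterion, it is also open whether it will be run at all.

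**Working it through.** **Inputs** (Sample size section): SD of follow-up PAEE 15.4 kJ/kg/day, baseline to follow-up correlation 0.69, target difference 4.1 kJ/kg/day, significance level 1.67%, power 80%, 465 completers, 20% attrition, about 580 randomised. A two-sided test is assumed. Allocation is 1:1:1.

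**1. Reproducing the plan's figure.** Residual SD after baseline adjustment = 15.4 × √(1 − 0.69²) = 11.15. Completers per arm = 2 × (2.393 + 0.842)² × 11.15² / 4.1² ≈ 154.7, so 155, and 3 × 155 = 465, as stated. Then 465 / 0.80 ≈ 581, or 582 rounded up, which fits the stated 580. The sample size is sound and is not affected by this point.

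**2. Precision of one contrast.** SE = √(2 × 15.4² × (1 − 0.69²) / 155) = 1.27. The smallest significant difference is 2.393 × 1.266 = 3.03 kJ/kg/day.

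**3. Bias under an assumed shift.** Suppose non-completers in arm k differ by s_k from what the completers' regression predicts, and a proportion p_k is missing. The bias of a complete-case contrast is then, in size, p₁s₁ − p₀s₀.

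With 20% missing, a shift in one arm only, and no true effect:

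| Assumed shift (kJ/kg/day less active) | Bias = 0.20 × shift | Share of 4.1 | Bias / SE | False-positive rate (nominal 1.7%) |
|---|---|---|---|---|
| 2 | 0.4 | 10% | 0.32 | 2.2% |
| 5 | 1.0 | 24% | 0.79 | 5.5% |
| 10 | 2.0 | 49% | 1.58 | 21% |

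The rate is Φ(−2.393 + bias/SE) + Φ(−2.393 − bias/SE).

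If shift and loss are equal in both arms, the bias is (0.20 − 0.20) × s = 0. If the shift is equal but loss is 30% against 10%, the bias is (0.30 − 0.10) × s = 0.20 × s, the same as in the table.

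**4. Would imputation show it?** This was simulated with 1,500 two-arm trials of 193 per arm, no true effect, and the SD and correlation above. About 20% were missing overall; dropout followed a logistic model. Where an auxiliary post-intervention variable was used, its residual correlation with the outcome was assumed to be 0.3. Mean estimated differences in kJ/kg/day (Monte Carlo SE about 0.03):

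| Dropout depends on | Complete case | Imputation, ANCOVA variables | Imputation with auxiliary |
|---|---|---|---|
| Arm only (30% v 10%) | −0.04 | −0.03 | −0.04 |
| Baseline PAEE, in one arm | 0.07 | 0.07 | 0.07 |
| Auxiliary variable, in one arm | 0.58 | 0.58 | −0.01 |
| Unseen outcome, in one arm | 1.94 | 1.94 | 1.78 |

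The first two rows show no bias; the full data in the second gave 0.06. In the last row about 21% and 20% were missing, and complete-case ANCOVA rejected in 20% of trials against a nominal 1.67%. That scenario corresponds to a shift of about 1.94 / 0.207 = 9.4 kJ/kg/day, close to the largest shift in step 3, and the two calculations agree.

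**The case against.** The strongest reply is that the article does not name the imputation variables. Intentions, perceived risk and anxiety are all measured immediately after the intervention, and the third simulated scenario shows that imputation using such a variable can remove the bias it explains and so expose it. The imputation model may be set out in an analysis plan that is not shown. This stands. A reader might infer that the planned imputation tests nothing and could reveal no bias of any kind; the documents do not support that. The limit applies to imputation with the ANCOVA variables, and otherwise to whatever the added variables leave unexplained. In the fourth scenario that was most of the bias: 1.78 of 1.94 remained.

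A reader might also infer that any difference in dropout between arms biases the result. It does not. Dropout related to arm alone, or to arm and baseline PAEE, left the baseline-adjusted estimate unbiased.

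The mechanism need not be confined to one arm. Two of the three arms receive a risk estimate, and all three are encouraged to be active, so shifts could be similar and cancel. This stands as well, and is why the shifts must be treated as assumptions. A shift of 10 in one arm only is about 0.9 residual SD (10 / 11.15) and sits at the unfavourable end. The 20% is a planning allowance, not a forecast.

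There are safeguards. Everyone invited has already worn the monitor for at least three full days, the wear period is arranged by telephone, non-responders are chased, and reasons for loss are summarised. These may reduce attrition and help interpretation, but none measures how far the treatment contrast would move.

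Finally, the absence of a delta-adjusted analysis from an article is not in itself a fault. The point rests on what the article does state: a conditional check, and an assumption shared with the analysis being checked.

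**Conclusion.** The point holds in a limited form. The only stated sensitivity analysis for missing primary outcomes has no trigger and keeps the missing-at-random assumption. With the ANCOVA variables it essentially repeats the complete-case result. It therefore cannot show bias from outcome-related dropout that differs by arm, beyond what any added imputation variables explain.

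Under assumed one-arm shifts of 2 to 10 kJ/kg/day at the planned attrition, the possible bias runs from a tenth to about half of the target difference, and it is nil if shift and loss are balanced. The documents give no figure for the true shift, so they do not show that the trial will be biased. They show that the stated check could not settle the question. The change is worth making because it is cheap and the trial is open.

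**What to change.** Delete the words *If necessary*, so that the sensitivity analysis is always run and reported, and specify two parts:

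1. Multiple imputation of PAEE carried out by arm, with the immediate post-intervention measures already collected (intentions, perceived risk, anxiety) as auxiliary variables.
2. A delta-adjusted analysis in which imputed PAEE is shifted by 0 to −10 kJ/kg/day, varied separately by arm and including equal shifts, reporting the shift at which the conclusion changes.

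The cost is a few extra analysis runs and a short table or figure. No new data are needed, and the sample size is unchanged.

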Participants of the Fenland Study are invited to take part in the DRCT if they have given permission to be contacted regarding potential involvement in future studies. Furthermore, they must have provided sufficient data to calculate their genetic and phenotypic risk estimates for T2D (described in detail below), and have worn the combined heart rate monitor and accelerometer for three or more full days without experiencing a severe skin reaction. Lastly, the monitor must have recorded at least 36 hours of complete data. Fenland Study participants who fulfil the inclusion criteria are invited to take part in the DRCT in the order in which they completed their health assessment (median 1.76 years prior to being invited), beginning with the most recent first. Potential participants are mailed an invitation letter, a study brochure, a sample consent form, and a response form. Those interested in taking part are asked to complete the response form and to return it in the enclosed freepost reply envelope. In the event of non-response, a second mailing is sent approximately four weeks after the first. Responders are excluded from the DRCT if they have been diagnosed with diabetes or are actively participating in another study. The exclusion criteria are explicitly stated in both the invitation letter and the study brochure, and are assessed in the response form via self-report.

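### The missing-indicator rule for baseline data is worded widely enough to cover the exploratory moderator and mediator models, where it can attenuate an interaction or leave residual confounding

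*Protocol article*

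**What the plan says.** One paragraph of the Statistical analysis section sets the missing-data rules. It opens with "All trial analyses will be performed on an intention-to-treat basis", excludes participants without outcome data, and keeps multiple imputation for missing outcome values in a possible sensitivity analysis of the primary outcome. It closes with the rule for baseline data: "Participants with missing baseline data will be included in the analyses using the missing-indicator method". No analysis is exempted.

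The next paragraph describes the primary ANCOVA, which asks whether "differences exist in mean PAEE at follow-up, adjusted for baseline, between randomised groups". It then says: "Exploratory analyses will be conducted to examine potential moderators and mediators of the intervention effects on PAEE". The variables listed are "sex, age, body mass index, time since the Fenland Study, and baseline measurements of the trial outcomes". A separate subgroup analysis compares high and low risk estimates.

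The article gives no expected rate of missing baseline data, no fill value, no statement on interactions with the indicator, and no confounder set for the mediator models.

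**The concern.** The missing-indicator method replaces a missing covariate by a constant and adds a 0/1 flag. In a randomised comparison this does no harm, because the baseline covariate and its missingness are independent of arm. Two of the planned model types lack that protection.

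- **Mediator models.** The path from mediator to PAEE is observational. For participants whose confounder is missing, the flag adjusts only for group membership, so within that group the confounder is uncontrolled.
- **Moderator models.** If the flag enters only as a main effect, the arm-by-moderator term treats participants with missing values as if they truly had the filled value. Where that value is far from the mean, they become high-leverage points that carry no information on the interaction.

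At stake are the exploratory answers on mechanism and on who responds. The Discussion names analysis of mediators and moderators as something that larger trials of this kind make possible.

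**Working it through.** **The plan's own figure.** The sample size is not in dispute; it sets the scale for the simulations. Inputs from the Sample size section are SD 15.4, correlation 0.69, difference 4.1, and a calculation "with a significance level of 1.67% and 80% statistical power".

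- Adjusted SD = 15.4 × √(1 − 0.69²) = 11.15.
- n per arm = 2 × (2.394 + 0.842)² × (11.15/4.1)² ≈ 155 (two-sided), and 3 × 155 = 465.
- 465/0.80 = 581.25, in line with the stated 580 or so.

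All simulations below use two arms of 155 and an assumed residual SD of 10.

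**Randomised comparison.** With 2% to 20% of a baseline covariate missing and handled by the indicator, the mean estimate of a true arm effect of 2 was 1.96 to 2.04. There is no material bias.

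**Moderator model.** Let m be the fraction missing completely at random, the fill value 0, arms equal, and no arm-by-indicator term. The fitted interaction is then the regression of the individual arm effect on the filled moderator:

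- covariance = (1 − m) × slope × SD²
- variance = (1 − m) × (SD² + m × mean²)
- ratio to the true slope = 1/(1 + m × (mean/SD)²)

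For another fill value, replace the mean by its distance from that value. A mean fill gives 1.00.

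| mean/SD (assumed) | m = 2% | m = 5% | m = 10% |
|---|---|---|---|
| 1.5 | 1/1.045 = 0.96 | 1/1.1125 = 0.90 | 1/1.225 = 0.82 |
| 3 | 1/1.18 = 0.85 | 1/1.45 = 0.69 | 1/1.90 = 0.53 |
| 5 | 1/1.50 = 0.67 | 1/2.25 = 0.44 | 1/3.50 = 0.29 |

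Simulation with a fill 3 SD from the mean and a true interaction of 2 gave 1.73, 1.39 and 1.06 at 2%, 5% and 10%, which are ratios of 0.87, 0.70 and 0.53. With a mean fill the estimates were 1.98 to 2.09, and with an arm-by-indicator term 1.96 to 2.04; both ranges include runs where missingness depended on the moderator. The closed form needs values missing completely at random. When the chance of missingness rose with the moderator and the fill lay on the opposite side, attenuation was worse: 0.98 for a true 2, where a participant at the mean had a 5% chance of being missing.

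If several correlated moderators enter together, the arm-by-indicator term is not enough. With the true interaction of the observed moderator equal to 0 and a correlated co-moderator 20% missing, the estimate was 0.36, against 0.01 with full data.

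**Mediator model.** Assumed: confounder C with SD 1; mediator = 0.5 × arm + 0.6 × C + noise of SD 0.8; PAEE depends on C with coefficient 4 and on the mediator with coefficient 2. Omitting C gives 2 + 4 × 0.6/(0.36 + 0.64) = 4.4. With the indicator, the large-sample value is 2 + 2.4 × m/(m + 0.64 × (1 − m)). The fill value does not appear in it.

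| m | formula | simulation |
|---|---|---|
| 2% | 2 + 0.048/0.647 = 2.07 | 2.07 |
| 5% | 2 + 0.120/0.658 = 2.18 | 2.19 |
| 10% | 2 + 0.240/0.676 = 2.36 | 2.35 |
| 20% | 2 + 0.480/0.712 = 2.67 | 2.69 |

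Complete cases gave 2.01 to 2.04.

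**Which variables are exposed.** Recruitment requires that "they must have provided sufficient data to calculate their genetic and phenotypic risk estimates for T2D", and the phenotypic estimate is built from age, sex and body mass index among other items. It also requires that "the monitor must have recorded at least 36 hours of complete data", so baseline PAEE should be almost complete. Time since the Fenland Study is a matter of dates. The high/low risk subgroup uses estimates that every participant must have. What remains is the self-completed baseline questionnaire scores and the Fenland food-frequency data.

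**The case against.** The strongest reply is that the article does not specify the harmful step. Attenuation of the interaction needs both a distant fill value and omission of the arm-by-indicator term, and the text fixes neither. With a categorical moderator such as self-rated health, missing can be its own level, and its interaction with arm then supplies that term. Such coding may well be settled in an analysis plan that is not shown. This stands: a reader might infer that the stated rule shrinks interactions, but the documents do not support that. The rule only leaves it possible.

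A second reply is that the sentence never names the moderator or mediator models and comes before they are introduced. That is true, but the wording is unrestricted, it closes a paragraph that opens by governing every trial analysis, and no other handling of missing baseline data is given. Covering those models is the natural reading.

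A third reply is that most listed moderators are complete by eligibility or design, that baseline questionnaires are collected before randomisation with a reminder, and that these analyses are exploratory and absent from the stated objectives. All of this stands and lowers the priority. The only mean/SD the article supports is 46.2/15.4 = 3.0 for follow-up PAEE in the study used for the sample size, and baseline PAEE is hardly ever missing here, so the ratios above are illustrative.

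The mediator example also assumes a strong confounder, yet the bias is only 0.07 on a true 2 at 2% missing. What does not fall away is that this bias cannot be removed by choosing a better fill value.

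A reader might also carry the criticism over to the primary result. That would be wrong: randomisation protects the adjusted comparison of arms.

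**Conclusion.** The concern holds as a rule drawn too widely. For covariate adjustment in the randomised comparisons the missing-indicator method is appropriate, and neither those results nor the sample size is touched.

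In mediator models it leaves residual confounding that is small at low missingness and grows with it: 2.07 to 2.69 for a true 2 across 2% to 20% missing, under the assumed confounder. In moderator models it can attenuate an interaction, by a factor of 0.90 to 0.69 at 5% missing for mean/SD of 1.5 to 3, but only with a zero fill, no arm-by-indicator term and values missing completely at random. With a mean fill or the extra term the factor is about 1.00.

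The missing rate, mean/SD, fill value and effect sizes are all assumptions, because the article gives none for these variables. Exposure is largely confined to baseline questionnaire and food-frequency scores in exploratory analyses, so this is a low-priority, inexpensive improvement.

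**What to change.** Restrict the rule in the Statistical analysis section along these lines:

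- Use the missing-indicator method only for covariate adjustment in the randomised comparisons of PAEE and the secondary outcomes.
- In each moderator model, include participants with that moderator observed, or add the arm-by-indicator term. If correlated moderators are fitted together, prefer participants with all of them observed.
- In mediator models, handle missing baseline covariates by multiple imputation, which the plan already names for outcomes, or by complete cases.

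The cost is a sentence or two of analysis wording. A few participants drop out of exploratory models, or there is a little more imputation work; how many are affected depends on a missing rate that the article does not give. Data collection, sample size and the primary analysis do not change.

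### The primary ANCOVA adjusts only for an old baseline PAEE and leaves sex, age, BMI and time since the Fenland Study to exploratory analyses, so it forgoes precision that costs almost nothing

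*Protocol article*

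**What the plan says.** Under Statistical analysis, the primary comparison is set out as follows: "An analysis of covariance (ANCOVA) regression model will be used to determine if differences exist in mean PAEE at follow-up, adjusted for baseline". The Methods part of the abstract likewise describes follow-up values adjusted for baseline. No other covariate is attached to the primary model. The same section names sex, age, BMI, time since the Fenland Study and baseline outcome measures as candidates for exploratory moderator and mediator analyses.

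Baseline PAEE comes from the Fenland health assessment, "median 1.76 years prior to being invited" (Recruitment). The Baseline assessment section and Table 1 show that the trial's own baseline stage is a questionnaire, with no second monitor wear.

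The Sample size section takes its inputs from the FAB study: "The mean (standard deviation) PAEE at follow-up in the FAB study was 46.2 (15.4) kJ/kg/day", and "the correlation between baseline and follow-up was high (0.69". The target is to "detect a between-group difference of 4.1 kJ/kg/day in PAEE at follow-up", "with a significance level of 1.67% and 80% statistical power". This leads to about 465 completers and about 580 randomised.

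**The concern.** ANCOVA gains precision to the extent that its covariates predict the outcome. Here the only covariate is a measurement that, at the median, is about 1.9 years old when the outcome is taken (1.76 years plus eight weeks, 8/52 = 0.15), before any mailing time is counted. When the one baseline is this old, other prognostic variables may still have something to add.

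The plan has such variables. Age, sex, height and weight were collected in the Fenland Study, and participants must have enough data for the phenotypic risk estimate to be eligible, so these should be essentially complete. Time since the Fenland Study is already a planned variable. All four are fixed before randomisation, so adjusting for them is safe.

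The trial is sized with no slack: 155 completers per arm gives 80.1% power at the planning values. A modest gain in precision, or a modest loss, would therefore show in the power.

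**Working it through.** **Inputs from the Sample size section.** Difference δ = 4.1 kJ/kg/day; SD σ = 15.4; correlation r = 0.69; α = 1.67% (0.05/3). The section does not state sidedness; two-sided is assumed because it reproduces the plan's figure (one-sided gives 393). Allocation is 1:1:1.

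**Reproducing the plan's figure.**

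n per arm = 2σ²(1 − r²)(z₁₋α/₂ + z₀.₈₀)² / δ²

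- 1 − 0.69² = 0.524, so the residual SD is 15.4 × √0.524 = 11.15.
- z values are 2.394 and 0.842.
- n = 2 × 15.4² × 0.524 × (3.236)² / 4.1² ≈ 155 per arm, and 3 × 155 = 465. This matches.
- 465 / 0.80 = 582, consistent with about 580.

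With no baseline adjustment the same formula gives 296 per arm, or 888. The baseline term therefore carries 888 − 465 = 423 completers' worth of precision.

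**What extra covariates could add, and what a different r would do.**

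Power = Φ(δ / √(2σ²(1 − r²)k / 155) − 2.394), where k = 1 for baseline only and k = 0.9 if the added covariates remove 10% of residual variance.

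The documents do not say how much sex, age, BMI and time since Fenland explain beyond baseline PAEE, so the 10% is an assumption. The values of r below 0.69 are also assumptions.

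| r | Residual SD | Power, k = 1 | Detectable difference, k = 1 | Power, k = 0.9 |
|---|---|---|---|---|
| 0.69 (plan) | 11.15 | 80.1% | 4.10 | 84.6% |
| 0.60 | 12.32 | 70.4% | 4.53 | 75.6% |
| 0.50 | 13.34 | 62.3% | 4.90 | 67.7% |

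The correlation could also be higher: at r = 0.75, power with baseline only would be 87.5%.

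**Sensitivity to the assumed gain, at r = 0.69.** If the covariates explain a further 2%, 5% or 10% of *total* outcome variance, power is 81.8%, 84.4% or 88.6%. A cut of 10% in *residual* variance equals 0.10 × 0.524 = 5.2% of total variance, so it lies near the middle of that range. It is worth the same as raising completers from 465 to 465 / 0.9 ≈ 517, about 52 more.

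**Limits of the remedy.** To restore 80% power, the added covariates would have to explain a further 0.116 of total variance if r were 0.60 (0.4761 − 0.36), or 0.226 if r were 0.50 (0.4761 − 0.25). They would be unlikely to make good a large fall in r by themselves.

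**The case against.** The strongest reply is that nothing here is wrong. ANCOVA on a pre-randomisation baseline is valid whatever the age of that baseline. The sample size assumes the same baseline-only model, so plan and calculation agree. Chance imbalance between arms is already reflected in the standard error. Baseline-only adjustment is a common, parsimonious choice, and a fuller analysis plan might list more covariates. All of this stands, except that the article is not silent: it states the primary model and assigns the other variables to exploratory work. That is a choice open to comment, and the gain from changing it is available even if r is exactly 0.69.

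A reader might go further and infer that the trial is underpowered because 0.69 cannot hold over so long a gap. The documents do not support this. The FAB interval is not given, the section defends the source by its similar population and identical outcome, and r here could equal or exceed 0.69.

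A reader might also infer that the baseline is poor because "the monitor must have recorded at least 36 hours of complete data". That is only the eligibility floor. Participants were told to wear the monitor for six days and nights, and must have worn it for at least three full days. Inviting the most recently assessed people first also limits the gap.

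Finally, a seasonal mismatch between the two wears is conceivable, but the article reports nothing about it, nor about how the baseline's predictive value changes with time.

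**Conclusion.** The point holds as a matter of efficiency. The primary model omits four pre-randomisation covariates that are already in hand, in a trial planned at 80.1% power. There is no bias and no arithmetic error.

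The size of the gain is not known from the documents. For illustration, a 10% cut in residual variance would move power from about 80% to 85% at r = 0.69. The lower power figures of about 70% and 62% are conditional on assumed correlations of 0.60 and 0.50; they show how far the design leans on the borrowed value and are not a forecast.

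**What to change.** In Statistical analysis, prespecify the primary model as follow-up PAEE on randomised arm, baseline PAEE, sex, age, BMI (as measured in the Fenland Study) and time from the Fenland assessment to randomisation. The exploratory moderator analyses can stay as they are. The cost is a sentence of wording and a few degrees of freedom out of about 465; no new data are needed.

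Optional additions:

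- An interaction of time since Fenland with baseline PAEE, and terms for season. If season at follow-up is included, define it from the randomisation date or the originally scheduled wear date. The actual wear date can be rearranged by the participant after allocation, so it is not a pre-randomisation variable.
- A sentence in Sample size saying that 80% power is conditional on r = 0.69 from the FAB study, giving that study's interval, and showing power at 155 per arm over a stated range such as 0.50 to 0.69.
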